## Discussion

Accurate staging is the foundation of prognostic outcomes in oncology and has an immediate effect on patient care in every phase of disease. Although the quality of imaging has improved considerably over the past decades, the search for optimized modalities for specific indications continues. Although the recent introduction of PET-MRI combines the major advantages of both techniques, the value of PET-MRI in staging for the oncological patient still has to be proven. Ours will be the first study to assess the value of PET-MRI in the follow-up of thermal ablation of CRLM.

Early diagnosis of small volume recurrences is the primary goal of intense surveillance strategies following local hepatic tumor ablation. Treatment of these LTP and of new intra-hepatic lesions may allow complete tumor eradication and therefore provide potential cure in patients treated for CRLM
[5]. To detect recurrent disease at an early stage, we advocate a local surveillance protocol with intensive follow-up over the 12-month period in which most recurrences occur
[4]. Although numerous studies have attempted to define an optimal imaging algorithm after local treatment of liver metastases, the frequency, duration and survival benefit of surveillance have not yet been formally proven and general consensus is lacking
[22,23]. To the best of our knowledge, no prospective studies comparing follow-up schemes after RFA or MWA have yet been published.

PET-CT has proven value in the imaging-based diagnosis of recurrent disease following RFA/MWA of liver malignancies, and repeat treatment is often initiated solely based on this imaging modality.

The importance of histological proof of malignancy of a recurrence detected by imaging has long been a subject of debate within the thermal ablation field. We will therefore take multiple biopsies of the suspected area, taking into account the possibility of sampling necrotic tissue rather than active tumor tissue (sampling error). A sampling error of this type may influence our calculation of the specificity of PET-MRI, because false-positive results cannot be completely ruled out. The reference standard (in addition to pathology) for imaging accuracy will be the presence or absence of recurrent disease at clinical follow-up in the first year.

The period between FDG injection and acquisition of the PET-CT in this study is 30 minutes longer than the standard protocol, which might increase our ability to detect intrahepatic malignancies. Background activity in the normal liver parenchyma due to high glucose metabolism and abundant expression of Glut-1 and Hexokinase II can often impede detection of liver lesions. Following a rationale that FDG accumulates over time in malignant cells as compared to healthy or inflamed hepatocytes, several authors have proposed that PET-CT imaging may improve lesion detectability over time through an improvement in the tumor-to-background ratio
[24,25]. It is known that FDG uptake by a tumor may not plateau before 90–120 minutes and peak levels may persist for up to 4 hours after injection
[26]. Using target-liver ratios, we will investigate whether the 30 minutes delay between both PET-scans contribute to an improved differentiation of post-ablation inflammation and residual tumor
[15]. The study has not been designed to provide semi-quantitative values for FDG uptake as predictors of therapeutic response, generally expressed as the standard uptake volume (SUV). However, the SUV can vary considerably and the time lapse between FDG injection and acquisition is a major contributor to this variation
[27].

Follow-up is only worthwhile when patients comply to a physician’s recommendations, and compliance with medical advice has been a challenge since first described by Hippocrates
[28]. Numerous factors determine whether a person’s behaviour coincides with medical advice, such as the duration of therapy, the complexity of the regimen and psychosocial factors
[29]. Adherence to follow-up can also be affected by a patients’ negative experience of examinations such as discomfort and pain
[30,31]. These patient preferences may contribute to final decision making on follow-up imaging, especially when modalities are known to be equally effective. We formulated the hypothesis that PET-MRI provides a less favourable experience when compared to PET-CT, as the MRI examination may elicit anxiety due to the need to remain immobile and alone while enclosed in the MRI tunnel for a prolonged period of time, in addition to the noise associated with the examination
[32].

In this study, we solely focus on the ability of PET-MRI to identify intrahepatic recurrences, since most recurrences after local treatment of the liver reoccur in the liver
[1,2]. However, a large group of patients will eventually develop extrahepatic metastases or a local recurrence at the site of the primary tumor. These are important predictors of overall survival since they determine whether local hepatic recurrences can still be treated
[5]. PET-CT is currently the modality of choice to rule out extra-hepatic disease
[33], but if PET-MRI proves to be effective in local follow-up future studies should focus on extrahepatic follow-up and the ability and feasibility of PET-MRI to detect metastatic lesions throughout the body. In addition, randomised controlled trials should be performed to compare PET-CT and PET-MRI, or when one of the techniques has proven to be significantly superior, an intense versus a less intense follow-up protocol after thermal ablation of CRLM and the effect on overall survival.

PET-MRI is currently only available in highly specialized hospitals. Before general implementation can be pursued, the potential and limitations of this modality need to be thoroughly investigated. In the current climate, associated costs also play an important role in the implementation of diagnostic and treatment methods in daily patient care. We are aware of only one study to date that has addressed the cost-effectiveness of PET-CT after RFA of hepatic malignancies
[10]. These authors showed that PET-CT is more cost-effective than independent use of CT or MRI. However, as no study has yet addressed the cost-effectiveness of using PET-MRI, long-term cost-effectiveness, the results of future treatment and the yield of different scan-moments all need to be assessed.

This study will contribute to the search for an optimal follow-up protocol for patients treated with RFA or MWA for CRLM. As minimally invasive procedures become increasingly important in the treatment of the oncologic patient, adequate staging of disease is essential for optimal treatment results. This study may contribute to improved staging and consequently to the effective treatment of this ever-expanding patient group.

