### Primary and secondary objectives

We will assess the effectiveness of FDG PET-MRI in the follow-up of thermal ablation (RFA/MWA) of CRLM. Our primary aim will be to assess the accuracy of FDG PET-MRI in the diagnosis of local progression in the first year after RFA/MWA of CRLM. Therefore, all FDG PET-MRI images will be compared to FDG PET-CT and 4-phase liver CT images, which are the current standard of care. Results of different imaging sets will be compared on a per-patient and a per-lesion base. These results will then be compared to a reference standard: either histological outcome (if available) or clinical follow-up.

Secondary outcomes will include the accuracy of diagnosis of new intrahepatic disease after RFA/MWA. Since only a single 18 F-FDG per combined PET-MRI and PET-CT visit will be applied, we will have the opportunity to investigate whether dual-time point PET can increase the specificity of the 18 F-FDG signal and increase diagnostic accuracy
[15]. The reproducibly and robustness of inter-observer variation will also be determined. Clinical relevance will be studied by recruiting a panel consisting of a radiologist, interventional radiologist, nuclear medicine physician, oncologist, oncological surgeon and a radiation oncologist to retrospectively review PET-MRI images and agree on the preferred treatment. Choice of treatment based on PET-MRI will then be compared to the treatment that was actually received based on PET-CT and 4-phase liver CT. Finally, patients’ preferences will be assessed at one year follow-up using a specifically designed questionnaire that compares both modalities (Table 
1).

**Table 1 T1:** Questionnaire comparing PET-CT and PET-MRI (completed following fourth PET-MRI)

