### Image analysis

Only PET-CT and 4-phase liver CT images will be analysed and used in the context of routine patient care during clinical follow-up. The PET-MRI images will not be part of the diagnostic and follow-up process.

For imaging analysis, blinded data sets of all scans will be viewed both separately and independently by two designated, experienced radiologists and two nuclear medicine physicians. The reviewers will be blinded to the results of the other imaging modalities and to final patient outcome. A time-interval of at least four weeks will be introduced between the first and second review. Progressive disease will be scored on a per-patient and per-lesion basis, and results of all imaging modalities will be compared. The criteria for progression on different modalities are defined in Table 
3. Each lesion on each modality will be scored on a separate form and results will be scored from 1–5 (Table 
4) and size and location of the lesions will be reported. A LTP is defined as a lesion located in or within 1 cm of the ablation zone; a new intrahepatic lesion is defined as a lesion located more than 1 cm distant from the ablation zone
[6]. On MRI, a suspicious lesions has to meet the definition of LTP in at least two different sequences before it is considered positive for progression.

**Table 3 T3:** Test positivity criteria for progressive disease on different imaging modalities; ≤1 cm of the ablation zone (LTP) / >1 cm of the ablation zone (new intrahepatic recurrence)

ceCT		Newly detectable hypodense lesion
MRI	T1	New focal hypo-intense lesion
	T2	New focal hyper-intense lesion
	Contrast enhanced	Irregular peripheral enhancement pattern of a circumscribed lesion
	Diffusion weighed	Lesion with high signal intensity on b800
FDG PET		Lesion with clearly increased focal uptake as compared to liver background

**Table 4 T4:** Study form for reviewers’ results (per lesion base)

**Study number:**		**Reviewer number:**
**Score**	**Definition**	**Explanation**
1	Normal	Confident that no tumor recurrence is present in the ablation zone/confident that no new intrahepatic lesions are present
2	Probably benign	The appearance of the ablated lesion is compatible with post-ablational inflammation or rim-like characteristics/the new lesions diagnosed do not appear malignant

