### Recurrent disease and repeated treatment

If recurrent disease is suspected on either 4-phase CT of the liver or on PET-CT, the patient will be evaluated for re-treatment by our multidisciplinary liver board. If either resection of a LTP or chemotherapy is indicated, the patient will be excluded from further participation in the study. If patients are eligible for repeated RFA/MWA treatment of the LTP, study participation will be continued. Patients with new intrahepatic lesions that are eligible for local treatment (surgery or ablation) will remain in the study, as long as the initially ablated area remains unaffected (Figure 
1). Prior to re-treatment with RFA/MWA, several biopsies will be taken from the suspected area for pathological confirmation. To minimize the chance of ‘track seeding’, tract ablation will be performed after the procedure. Extra-hepatic disease will be treated as deemed suitable. If there is any doubt as to whether an imaging feature indicates recurrent disease, the scan will be repeated after 3 months as a confirmation.

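### The reference window closes at the last study scan and only PET-CT and CT can trigger confirmation, so a true lesion seen only on PET-MRI at month 12 counts as a PET-MRI false positive

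*Protocol article*

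**What the plan says.** The reference standard appears in two places in the protocol article. Primary and secondary objectives gives it as "either histological outcome (if available) or clinical follow-up". The Discussion adds the time limit. Alongside pathology, the standard "for imaging accuracy will be the presence or absence of recurrent disease at clinical follow-up in the first year". It is therefore a composite of pathology and first-year clinical follow-up.

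Image analysis says which imaging feeds that follow-up: "Only PET-CT and 4-phase liver CT images will be analysed and used in the context of routine patient care during clinical follow-up". It then adds: "The PET-MRI images will not be part of the diagnostic and follow-up process".

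Recurrent disease and repeated treatment sets the trigger for work-up: "If recurrent disease is suspected on either 4-phase CT of the liver or on PET-CT, the patient will be evaluated for re-treatment". Planned histology comes after that trigger: "Prior to re-treatment with RFA/MWA, several biopsies will be taken from the suspected area for pathological confirmation". For doubtful findings, "If there is any doubt as to whether an imaging feature indicates recurrent disease, the scan will be repeated after 3 months as a confirmation".

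PET-CT and 4-phase CT are also the tests with which PET-MRI is compared (Primary and secondary objectives). Scans are three-monthly for one year (Study procedure). The title of Table 1 refers to a fourth PET-MRI, which puts the last one at about month 12.

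**The concern.** The comparator tests supply all the imaging in the follow-up part of the reference standard, and they also control the route to planned histology. PET-MRI has no part in either. This is incorporation bias combined with differential verification: a lesion seen by PET-CT or CT can be worked up, whereas a lesion seen only by PET-MRI has to wait until PET-CT or CT also shows it.

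Waiting is possible after the month 3, 6 and 9 scans, because later PET-CT and CT fall inside the window. After month 9 only one more round remains. After month 12 there is none. At that visit a true lesion seen only on PET-MRI has no written route to confirmation and is classed as absent.

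The primary accuracy comparison is affected. So is the hypothesis, stated in the Background, that PET-MRI is superior in early detection of new intrahepatic lesions, because earlier detection at the last visit would be recorded as a PET-MRI error.

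**Working it through.** **1. The plan's own figure.** Sample size calculation uses n = 20 and p = 0.35 and gives an 88% chance of finding 5 events. Read as at least 5, P(X ≥ 5) for Binomial(20, 0.35) is 0.882, so the figure reproduces and is not in dispute. The expected number of events is 20 × 0.35 = 7, and the article treats 5 as the minimum for a meaningful comparison. With numbers this small, one misclassified patient is visible in the result.

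**2. What happens to a true lesion seen only on PET-MRI, by visit.**

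| First seen on PET-MRI at | Later PET-CT/CT rounds within year 1 | Can it become reference-positive? |
|---|---|---|
| Month 3 | 3 (months 6, 9, 12) | Yes, if a later PET-CT or CT shows it |
| Month 6 | 2 | Yes, same condition |
| Month 9 | 1 | Yes, with one opportunity |
| Month 12 | 0 | No written route |

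The 3-month repeat scan does not help at month 12. It belongs to the PET-CT/CT pathway, which PET-MRI cannot trigger, and it would fall at 12 + 3 = month 15, outside the window.

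**3. Illustration with one such lesion.** Assume 7 patients with local progression and 13 without, and no reading errors except that PET-CT misses one lesion, which PET-MRI sees at month 12.

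| | Against the truth | Under the stated window |
|---|---|---|
| PET-MRI sensitivity | 7/7 | 6/6 |
| PET-CT sensitivity | 6/7 (86%) | 6/6 |
| PET-MRI specificity | 13/13 | 13/14 (93%) |
| PET-CT specificity | 13/13 | 14/14 |
| PET-MRI overall accuracy | 20/20 | 19/20 |
| PET-CT overall accuracy | 19/20 | 20/20 |

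Overall accuracy reverses, a false specificity difference appears, and the sensitivity difference vanishes.

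**4. Dependence on how often it happens.** The documents give no frequency. Let f be the assumed share of true lesions missed by PET-CT that are never confirmed within the first year. Take sensitivities of 93% and 76% from the Background (fused PET-MRI against PET-CT, hepatic metastases in general), prevalence 0.35, perfect true specificity and conditionally independent tests.

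- Share of true lesions that become reference-positive: R = 0.76 + 0.24 × (1 − f)
- Apparent PET-CT sensitivity: 0.76 / R
- Share of true lesions seen only on PET-MRI: 0.93 − 0.93 × 0.76 = 0.223
- Apparent PET-MRI specificity: 1 − (0.35 × 0.223 × f) / (0.65 + 0.35 × 0.24 × f)
- Chance of at least 5 reference-positive patients: Binomial(20, 0.35 × R)

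| f | PET-CT sensitivity | PET-MRI sensitivity | Difference | PET-MRI specificity | P(≥ 5 reference-positive) |
|---|---|---|---|---|---|
| 0 | 76% | 93% | +17 points | 100% | 88% |
| 0.25 | 81% | 93% | +12 | 97% | 84% |
| 0.5 | 86% | 93% | +7 | 94% | 79% |
| 1 | 100% | 93% | −7 | 89% | 65% |

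If the two tests instead miss the same lesions as far as possible, PET-MRI specificity is 98%, 96% and 92% at f = 0.25, 0.5 and 1, and at f = 1 both sensitivities read 100%. The direction is the same. The value f = 1 is an extreme bound, since lesions first seen at months 3 to 9 can be confirmed later.

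**The case against.** **Keeping PET-MRI out of care is a deliberate choice.** It is reasonable for a modality under study, and histology or follow-up is a common reference. This stands, and the point does not ask for PET-MRI to enter care. The defect is the absence of follow-up after the last index scan.

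**Pathology is part of the reference.** True. But planned biopsies follow a PET-CT or CT suspicion, so they do not reach a lesion that only PET-MRI shows. A reader might infer that PET-MRI-only findings never receive histology. That goes too far: a lesion from months 3 to 9 may later appear on PET-CT or CT and be biopsied, and new intrahepatic lesions may go to surgery.

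**Readers are blinded.** Four reviewers score the scans without knowing the other modalities or the outcome. This protects the readings but not the reference. A reader might also infer that month-12 scans are judged by the same-day PET-CT. The article gives no adjudication rule for individual scans, so that is not established. What is established is that no later information falls inside the window.

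**CEA is also measured.** Only when it was elevated pre-operatively, and it cannot locate a lesion or separate local progression from a new lesion.

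**The illustration rests on one patient.** It does: one discordant pair gives an exact McNemar p of 1 in either direction, and sensitivity moves to a tie rather than reversing. It also uses local progression, where the stated hypothesis is at least equivalence; the superiority claim concerns new intrahepatic lesions. It shows the mechanism and does not predict the result.

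**Negative biopsies.** One might add that necrotic samples before re-ablation also tilt the comparison towards PET-CT and CT. The documents do not support this. Those biopsies follow a PET-CT or CT suspicion, so a falsely negative sample counts at least as much against those tests, and the Discussion already discloses the sampling problem.

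**Conclusion.** The point holds for the last visit. With the first-year window as written, a true lesion seen only on PET-MRI at about month 12 must count as a PET-MRI false positive while the PET-CT miss is hidden. For months 3 to 9 the problem is one of reduced opportunity for confirmation, greatest at month 9. The bias runs in favour of PET-CT and CT, and more patients would not remove it.

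Its size is uncertain. One patient is enough to reverse overall accuracy in the 7-in-20 illustration. On the article's 93% and 76%, with independent tests, the 17-point sensitivity advantage shrinks to 12 points if a quarter of PET-CT misses go unconfirmed and to 7 points if half do. These figures assume perfect true specificity and carry over sensitivities that were not measured for local progression. The last of the four planned rounds is a quarter of the scans, but that is not the share of lesions affected, which the documents do not give.

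**What to change.** In the reference-standard paragraph of the Discussion, and to match under Primary and secondary objectives:

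- Define the reference for each index scan as histology or follow-up information obtained after that scan.
- Extend the reference window past the last study scan, for example by 6 months, using routine records. This assumes that routine follow-up continues; the article describes only the first year, so this needs checking.
- Report accuracy without the month-12 index scans as a sensitivity analysis. It should not be the primary restriction, because it loses events. If 10% to 25% of local progressions first appeared at month 12 (an assumption), the event probability would be 0.35 × 0.90 = 0.315 to 0.35 × 0.75 = 0.2625, and the chance of at least 5 would fall from 88% to about 80% to 63%.
- At most, also report accuracy with negative pre-ablation biopsies counted both ways.

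The cost is record review for 20 patients and a later database lock. No procedure is added, and PET-MRI stays out of patient care.

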### Imaging

A summary of imaging steps is provided in Table 
2. PET imaging will be conducted according to EANM guidelines
[17]. 18 F-FDG will be administered while the patient is supine on the PET-MRI table using MR compatible devices. The MRI will be performed during the period in which FDG distributes throughout the body, and PET will commence approximately 60 minutes after FDG injection. The PET of the PET-CT will follow 20 minutes (±5) after completion of the PET-MRI, followed by a whole body low-dose CT for attenuation and image-fusion and a diagnostic 4-phase liver CT. This scanning sequence has been chosen to minimize the burden for the patient, to optimize reliability of the dedicated liver MRI sequences and to minimize the time between both PET scans.

**Table 2 T2:** Imaging protocol and timeline of PET-MRI and PET-CT (T = approximate time in minutes)

T = 0	Injection FDG	
T = 5	Start MRI	Axial T2-weighted imaging
		T1 in- and opposed phase GRE
		Diffusion-weighted imaging
		Fat-suppressed T1-weighted eThrive (contrast enhanced)
		- pre-contrast
		- arterial phase (bolus tracking)
		- portovenous phase (70 sec delay)
		- late venous phase (200 sec delay)
		Attenuation sequence (skullbase – midthigh)
		Whole body T1-weighted mDixon (skullbase – midthigh)
T = 60		PET skullbase – midthigh
T = 75	**End PET-MRI**	**Transfer to PET-CT**
T = 95	Start PET-CT	PET skullbase – midthigh
		low dose CT
		4-phase CT liver
		- pre-contrast
		- arterial phase (bolus tracking)
		- portovenous phase (70 sec delay)
		- late venous phase (240 sec delay)
T = 145	End PET-CT	

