#### 18F-FDG PET (PET-MRI)

After MRI, the PET-MRI table is turned and the patient is placed in the PET gantry. The PET features an 18 cm axial field of view, 9 cm overlap between bed positions and a 5.5 mm reconstructed isotropic spatial resolution. The scan trajectory covers the skull base to mid-thigh, taking 2 min/bed position. Reconstructed images have an image matrix size of 144X144, voxel size of 4X4 mm and slice thickness of 5 mm. Data are reconstructed by means of a Blob-OS-TF algorithm. Fusion images are created with the PET sequence and atMRI, mDixon axial and coronal whole body and axial T2 liver.

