#### 18F-FDG PET (PET-CT)

The Philips Gemini TF PET-CT system (Philips Medical Systems, Cleveland, Ohio, USA) is comparable to the PET unit of the PET-MRI. Scanning is started with a whole body PET (skull base to mid-thigh), with data being reconstructed by means of a raw action ordered subset expectation maximization algorithm using default reconstruction parameters. Time of flight (TF) information is used during reconstruction. Reconstructed images have an image matrix size of 144X144, a voxel size of 4X4 mm and a slice thickness of 5 mm. The acquisition time per bed position is adjusted for the time interval between the start of PET-CT and FDG injection and will usually be 2–3 min/bed position.

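### The dual-time-point FDG question changes PET system together with uptake time, so a late-minus-early result shows their joint effect and cannot be credited to delay alone

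*Protocol article*

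**What the plan says.** Under Primary and secondary objectives, the article uses the single FDG injection per visit to "investigate whether dual-time point PET can increase the specificity of the 18 F-FDG signal and increase diagnostic accuracy". The Discussion names the measure and the factor of interest: "Using target-liver ratios, we will investigate whether the 30 minutes delay between both PET-scans contribute to an improved differentiation". The differentiation meant is between post-ablation inflammation and residual tumour.

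The Imaging section fixes the order of the scans. On the PET-MRI, "PET will commence approximately 60 minutes after FDG injection". Then "The PET of the PET-CT will follow 20 minutes (±5) after completion of the PET-MRI". Table 2 starts the PET-MRI's PET at 60, ends that examination at 75 and starts the PET-CT at 95, under the caption note "T = approximate time in minutes".

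For the PET-MRI the article states: "Data are reconstructed by means of a Blob-OS-TF algorithm". For the PET-CT it describes a whole-body PET "with data being reconstructed by means of a raw action ordered subset expectation maximization algorithm using default reconstruction parameters", and adds that time-of-flight information is used. The same section calls the PET-CT system comparable to the PET unit of the PET-MRI. The Discussion recognises uptake time as a source of variation in SUV. It does not mention that the PET system changes at the same moment.

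**The concern.** A dual-time-point comparison isolates uptake time only if the rest of the measurement stays the same, or if its effect is known. Here the second time point also brings a second scanner, a differently named reconstruction and a different attenuation source.

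A target-liver ratio cancels any factor that multiplies lesion and liver equally, such as a global calibration difference. It does not cancel differences in resolution or local attenuation error. Those can act differently on a small focus than on uniform liver, and small-volume recurrences are what the surveillance is meant to find.

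At stake is a statement that delayed imaging improves specificity, or fails to, when part or all of the observed change may belong to the PET system.

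**Working it through.** **1. What changes between the two time points**

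| | Early PET | Late PET |
|---|---|---|
| System | PET of the hybrid PET-MRI | Gemini TF PET-CT |
| Nominal start (Table 2) | 60 min | 95 min |
| Reconstruction | Blob-OS-TF | ordered-subset EM, default parameters, time of flight used |
| Attenuation source | low-resolution MR attenuation sequence | low-dose CT |
| Time per bed | 2 min | usually 2–3 min, adjusted to the time since injection |
| Matrix; voxel; slice | 144 × 144; 4 × 4 mm; 5 mm | the same |

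**2. Can delay and system be separated?**

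For a lesion at a visit, write the ratio of target-liver ratios as

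observed (late / early) = delay effect × system effect.

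In a model of the log ratio, the indicator for late equals the indicator for PET-CT in every row. The two columns are identical, so only the product can be estimated.

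More data do not help. Twenty patients at four three-monthly visits give up to 20 × 4 = 80 paired examinations, all in the same order. They narrow the interval around the product without splitting it.

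**3. How far could the product mislead?**

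The documents give no system factor. Assume one of 0.90 to 1.10 acting on the target-liver ratio:

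- No delay effect (1.00): observed 1.00 × 0.90 = 0.90 to 1.00 × 1.10 = 1.10.
- True delay effect of 1.10 (also assumed): observed 1.10 × 0.90 = 0.99 to 1.10 × 1.10 = 1.21.

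Within this range a real 10% rise could vanish, or a 10% rise could appear from nothing.

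**4. Does it reach the tumour-versus-inflammation contrast?**

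- If the factor is the same for both lesion types, it multiplies both and leaves their ranking unchanged.
- If it differs, the contrast moves. With no delay effect and factors of 1.10 for tumour and 1.00 for inflammation, the relative separation appears to grow by 1.10 / 1.00 = 1.10.

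Table 3 describes progression on PET by focal uptake, and Table 4 lists rim-like features for a probably benign ablation zone. Different shapes make equal factors an assumption, but they do not show that the factors are unequal.

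**5. The stated delay**

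- Start to start: 95 - 60 = 35 min.
- With the tolerance: (75 - 60) + 20 ± 5 = 30 to 40 min.
- End of PET-MRI to start of PET-CT: 95 - 75 = 20 min.

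The Discussion's 30 minutes is not the nominal value on either reading. It is the lower edge of the start-to-start window.

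**The case against.** The article calls the two PET units comparable, and matrix, voxel size and slice thickness are identical. Both reconstructions may belong to the same family: the PET-CT method is an ordered-subset method using time of flight, and Blob-OS-TF can be read the same way, although the article does not spell that name out. Bed time on the PET-CT is adjusted for the time since injection, which offsets decay, so it is not good evidence of bias. Cross-calibration or harmonisation may stand in the full protocol, and its absence from a condensed article is no finding. The Discussion asks only whether delay contributes, the objectives section presents the question as an opportunity, and no test is attached to it under Statistical analysis.

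Most of this stands, and it limits the size of the point. It does not remove the aliasing. Equal voxel size does not make the attenuation sources equivalent, and cross-calibration mainly addresses global scale, which the ratio already cancels.

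A reader might infer more than the documents support:

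- **That the system difference is known to be large, or that the comparison is worthless.** No figure in the article shows how far the two systems differ, and a factor common to both lesion types would leave their ranking intact.
- **That the 30 versus 35 minutes causes the attribution problem.** It does not. Table 2 is approximate, 30 lies within 30 to 40, and the aliasing would remain with the delay stated perfectly.
- **That matched reconstruction would cure it.** It would leave the attenuation source and the scanner tied to time.

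**Conclusion.** The point holds in a limited form. Because the order is fixed and no lesion is planned to be imaged at both times on one system, an early-to-late change in target-liver ratio, or in the separation of tumour from inflammation, cannot be credited to delay alone. This follows from the design as described and needs no assumption about size. The size of the system effect cannot be derived from the documents; the 0.90 to 1.10 range is only illustrative, and the true factor could be close to 1.

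The delay mismatch is 5 minutes at the nominal times and is a wording matter. Severity is low: the question is secondary, and the accuracy of PET-MRI for local progression, the primary aim, does not depend on it.

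**What to change.** 1. Report the late-minus-early result as the joint effect of delay and PET system in all cases, and draw no conclusion about the effect of delay alone on specificity.
2. Where raw PET data are available, add a sensitivity analysis with matched reconstruction and smoothing. State that it leaves the attenuation-map and scanner differences in place. Use it for this question only, not for the primary reading, since matched settings may suit neither scanner best.
3. Use each examination's recorded injection and acquisition times. They describe the delay actually achieved; they do not separate it from the system.
4. Reconcile the Discussion's 30 minutes with Table 2, for example as about 35 minutes from PET start to PET start (30 to 40 with the tolerance).

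Items 1 and 4 are wording changes, and item 3 uses times that should be on file. Item 2 costs a second reconstruction and depends on raw data having been kept, which the article does not say. No extra dose, scan or reading is needed.
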